## Abstract

**Aim:**

Colorectal cancer is the second commonest cause of cancer death worldwide. Colonoscopy plays a key role in the control of colorectal cancer and, in that regard, maximizing detection (and removal) of pre‐cancerous adenomas at colonoscopy is imperative. GI Genius™ (Medtronic Ltd) is a computer‐aided detection system that integrates with existing endoscopy systems and improves adenoma detection during colonoscopy. COLO‐DETECT aims to assess the clinical and cost effectiveness of GI Genius™ in UK routine colonoscopy practice.

**Methods and analysis:**

Participants will be recruited from patients attending for colonoscopy at National Health Service sites in England, for clinical symptoms, surveillance or within the national Bowel Cancer Screening Programme. Randomization will involve a 1:1 allocation ratio (GI Genius™‐assisted colonoscopy:standard colonoscopy) and will be stratified by age category (<60 years, 60–<74 years, ≥74 years), sex, hospital site and indication for colonoscopy. Demographic data, procedural data, histology and post‐procedure patient experience and quality of life will be recorded. COLO‐DETECT is designed and powered to detect clinically meaningful differences in mean adenomas per procedure and adenoma detection rate between GI Genius™‐assisted colonoscopy and standard colonoscopy groups. The study will close when 1828 participants have had a complete colonoscopy. An economic evaluation will be conducted from the perspective of the National Health Service. A patient and public representative is contributing to all stages of the trial. Registered at ClinicalTrials.gov (NCT04723758) and ISRCTN (10451355).

**What will this trial add to the literature?:**

COLO‐DETECT will be the first multi‐centre randomized controlled trial evaluating GI Genius™ in real world colonoscopy practice and will, uniquely, evaluate both clinical and cost effectiveness.

## INTRODUCTION

Colorectal cancer (CRC) is the second commonest cause of cancer death worldwide killing >915 000 per year [1]. In the UK, CRC affects one in 15 men and one in 18 women in their lifetime [2]. Most CRCs develop via the adenoma–carcinoma sequence [3], with mutation of multiple proto‐oncogenes and tumour suppressor genes potentially contributing to malignant transformation [4, 5, 6]. Non‐adenomatous polyps (including sessile serrated lesions and hyperplastic polyps) also play a role, albeit more minor, in CRC development [7, 8]. Carcinoma development may be disrupted, and cancer prevented, by removal of pre‐malignant lesions.

### Post‐colonoscopy CRC and adenoma detection

Colonoscopy is the gold standard investigation to seek colorectal adenomas (or CRC). However, adenomas may be missed due to incomplete mucosal visualization or failure to detect a visible lesion. Tandem colonoscopy (where a patient undergoes back‐to‐back colonoscopies) has estimated the miss rate to be 22% for all polyps, with an inverse relationship of miss rate to polyp size [9]. Missed lesions can result in post‐colonoscopy CRC (PCCRC) [10]—CRC occurring within 3 years of a non‐diagnostic colonoscopy [11]—and small (<10 mm), flat adenomas are over‐represented amongst missed lesions [9, 12]. A low adenoma detection rate (ADR, the proportion of colonoscopies in which one or more adenomas is detected) correlates with a higher rate of PCCRC [12, 13, 14, 15, 16, 17], and each 1% increase in ADR correlates with 3% reduction in PCCRC incidence [14].

### Improving adenoma detection

Multiple interventions have been recommended to improve adenoma detection, including measures to improve technique (e.g., longer withdrawal time, patient position change), improvement of bowel preparation, and devices that attach to the end of the colonoscope to increase mucosal visualization [18, 19, 20, 21, 22]. Attempts to improve the ability to identify lesions on the visualized mucosa include high definition colonoscopes [23], colonoscopes with increased field of view [24] and enhanced image analysis such as virtual chromoendoscopy [25], although an extensive network meta‐analysis suggests that no single strategy or category of assistive technology has a clear advantage [26].

### Computer‐aided detection of colorectal lesions

Technological advances, alongside the finding that a second observer improves adenoma detection [27, 28, 29], have stimulated the development of computer‐aided detection (CADe) systems (essentially a virtual second observer). Most current CADe systems are based on convolutional neural networks [30, 31, 32, 33], a form of deep learning optimal for complex image analysis, in which the video feed from the colonoscope is analysed and processed in real time to generate an output that is useful to the operator [34].

### GI Genius™

GI Genius™ (Medtronic Ltd) is a convolutional‐neural‐network‐based artificial intelligence module (Figure 1) which integrates with most endoscopy systems from all major manufacturers. It indicates potential abnormalities by projecting a green box on the monitor (Figure 2) and emitting an adjustable‐volume audible alert, without perceptible lag. The colonoscopist may then inspect the highlighted area more closely and decide whether to ignore, biopsy or excise the putative abnormality. The first randomized controlled trial (in expert centres only) found that using GI Genius™ improved the ADR by 14% in patients presenting with gastrointestinal symptoms, undergoing surveillance colonoscopy and participating in a national CRC screening programme [35]. These findings have since been confirmed with non‐expert colonoscopists [36]; although this improves the generalizability of the findings, they were pooled from two separate trials, with no trial having yet studied expert and non‐expert practice simultaneously. Furthermore, no study has yet conducted an economic evaluation of CADe.

**FIGURE 1 codi16219-fig-0001:**
[figure not shown]
The GI Genius™ intelligent endoscopy module (©Medtronic Ltd)

**FIGURE 2 codi16219-fig-0002:**
[figure not shown]
A colonic polyp highlighted within a green bounding box by GI Genius™ (©Medtronic Ltd)

### COLO‐DETECT

COLO‐DETECT is a parallel arm, multi‐centre (Box 1) randomized controlled trial that will compare polyp detection during GI Genius™‐assisted colonoscopy (GGC) to detection during standard colonoscopy (SC), in the context of routine colonoscopy practice in the UK. This includes patients referred for reason of gastrointestinal symptoms or requiring surveillance colonoscopy (together henceforth referred to as the ‘symptomatic population’) or as part of the national Bowel Cancer Screening Programme (BCSP, the ‘screening population’). Whilst tandem colonoscopy studies have been used elsewhere in endoscopy studies, and require smaller sample sizes to demonstrate effect, it was felt that a parallel arm design was both more pragmatic and reflective of clinical practice and thus more in keeping with the ethos of the study, especially as the sample size required to demonstrate a significant difference in detection using a parallel arm design was not deemed excessive (see the section Sample size, below).

BOX 1List of COLO‐DETECT study sites (subject to potential new sites)**Table jats-table-wrap-1:** 

South Tyneside and Sunderland NHS Foundation Trust (Sponsor site), North Tees and Hartlepool Hospitals NHS Foundation Trust, South Tees Hospitals NHS Foundation Trust, Kettering General Hospital NHS Foundation Trust, University Hospitals of Morecambe Bay NHS Foundation Trust, Bolton NHS Foundation Trust, Royal Wolverhampton NHS Trust, Newcastle‐upon‐Tyne Hospitals NHS Foundation Trust, Northumbria Healthcare NHS Foundation Trust
NHS, National Health Service.

## METHODS

### Study objectives

The COLO‐DETECT primary, key secondary and other secondary study objectives are listed in Box 2. They represent the intention to thoroughly assess the clinical and cost effectiveness of the GI Genius™.

BOX 2COLO‐DETECT study objectives**Table jats-table-wrap-2:** 

Primary objective: to compare mean number of adenomas per procedure (MAP) between GGC and SC Key secondary objective: to compare ADR between GGC and SC Other secondary objectives are*: to determine whether there is a difference in MAP and/or ADR between GGC and SC within each of the screening and symptomatic populations to determine whether there is a difference in mean polyps per procedure (MPP) or polyp detection rate (PDR) between GGC and SC to ascertain the nature and distribution of all polyps in the colorectum, including location, size and morphology, comparing GGC and SC to ascertain if there is a difference in the detection rate of sessile serrated polyps (SSP) between GGC and SC to ascertain if there is a difference in cancer detection rate between GGC and SC (this includes polyps removed at colonoscopy and subsequently found to be cancerous, and lesions felt to be cancerous at the time of colonoscopy) to determine whether there is a difference in advanced adenoma detection rate (AADR) between GGC and SC to determine if there is a difference in caecal intubation rate, insertion time to caecum, total procedure time, withdrawal time in the absence of polyps, and colonoscopist‐assessed and nurse‐assessed patient comfort scores between GGC and SC to determine if there is a difference in patient experience between GGC and SC, utilizing a validated patient‐reported experience measure [37] to identify any projected difference in future post‐polypectomy surveillance colonoscopy workload, according to the application of national guidelines [38] to participant‐level polyp data comparing GGC and SC to compare MAP and ADR between BCSP and non‐BCSP colonoscopists, comparing GGC and SC to compare MAP and ADR between colonoscopists of differing experience levels, as indicated by lifetime procedure numbers and average annual numbers of procedures performed in the last 3 years to compare MAP and ADR for the first 20% of study participants scoped by each colonoscopist with the last 20% of participants to identify any changes in MAP or ADR throughout the study to compare baseline MAP and ADR of each colonoscopist (6 months pre‐study) with that colonoscopist's MAP and ADR during the study in the SC arm (to assess for a contamination effect) and for 6 months post‐study (to assess for dependence upon GI Genius™) to collect contemporaneous data on MAP and ADR for colonoscopists not taking part in the study to follow up patients to identify future outcomes related to colorectal polyps or CRC In addition, further secondary objectives are: to collect data that will allow subsequent health economic evaluation to determine the cost effectiveness of GGC compared with SC to undertake a process evaluation including investigation of user experience of GI Genius™ (see Box 3)
ADR, adenoma detection rate; BCSP, Bowel Cancer Screening Programme; GGC, GI Genius™‐assisted colonoscopy; SC, standard colonoscopy. *secondary objectives 2‐15 will be assessed across the whole study population and between the symptomatic and screening populations.

The primary and key secondary objectives will be assessed across the whole study population, as well as within the symptomatic and screening populations, and according to colonoscopist experience. Other important markers of detection will be measured (such as polyp detection rate and polyp distribution) as well as procedural factors, patient experience and measures of the impact of GI Genius™ on colonoscopy services (especially post‐polypectomy surveillance burden). Given the noteworthy lack of cost effectiveness analysis for most assistive strategies or technologies, data will be collected to enable the economic evaluation of the cost effectiveness of GI Genius™ to inform decisions concerning wider adoption. Additionally, in recognition that financial issues alone do not determine uptake of novel interventions, a process evaluation will be undertaken to appreciate issues potentially affecting adoption and utilization of the GI Genius™ (see Box 3).

BOX 3Description of planned process evaluation**Table jats-table-wrap-3:** 

Evaluating and adopting novel technology, especially high‐cost technology, is often a lengthy and convoluted process, involving multiple stakeholders with often differing and sometimes conflicting priorities. COLO‐DETECT will include a process evaluation [39] which will seek to understand user experience and fidelity in relation to GI Genius™; identify any moderating contextual factors and/or unintended consequences of using GI Genius™; and explore barriers and facilitators to wide‐scale implementation of the technology into clinical practice. This will include scrutiny of trial data (e.g., deviations from protocol) and semi‐structured interviews with a range of stakeholders including (but not limited to) clinician users of the technology, service managers, healthcare commissioners and guideline‐making bodies such as the British Society for Gastroenterology. This will serve as an exemplar for the process of evaluating and adopting novel technology into the National Health Service (NHS).

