Upon attending for colonoscopy, consent will be confirmed in writing and participants will complete the EQ‐5D‐5L health‐related quality of life questionnaire [40]. Participants will be randomized by recruiting staff 1:1 to GGC or SC [41] using a secure web‐based platform. Randomization will be stratified by age category (<60 years, between 60 and <74 years, ≥74 years), sex, study site and referral category (symptomatic or screening population). In the event of randomization platform unavailability, a coin toss will be used.

Standard colonoscopy represents standard care for colonoscopy at each study site. GGC incorporates all elements of SC and differs only in that the GI Genius™ will be turned on and activated for at least the whole of the inspection phase of withdrawal, although the investigators recommend to participating colonoscopists that the GI Genius™ is activated prior to the procedure. Procedural data will be recorded onto a Case Report Form (CRF). Post‐procedure, participants in both arms will undergo standard post‐colonoscopy care and discharge procedures for each site.

Prior to discharge participants will be given a patient experience questionnaire (the validated Newcastle ENDOPREM™ [37]) and a second iteration of the EQ‐5D‐5L to complete and return in a pre‐paid envelope. Follow‐up will cease upon completion of a post‐procedure review between days 14 and 21. This may include accessing medical records (including endoscopy reports and histology) and a telephone call to assess whether any adverse events (AEs) or serious adverse events (SAEs) have occurred. No further contact will be required for study participation, although participants will be asked to consent to long‐term (up to 5 years) passive follow‐up of health outcomes through endoscopy data, medical records and national databases such as the National Cancer Registry Database, Hospital Episode Statistics data, National Endoscopy Database [42] and link to the CORECT‐R data repository [43]. Where data are currently anonymized participant consent will be sought to link data when this becomes possible. Present and future clinical care will be unaffected by study participation.

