### Sample size

The primary outcome for COLO‐DETECT is the difference in MAP between GGC and SC (for which a clinically meaningful mean difference has been considered to be 0.50 for screening patients and 0.30 for symptomatic patients) (based on communications between the senior author, the clinicians involved in the trial and taking opinion from other experts). Due to the importance of ADR in detection studies and its historical widespread use it is important that this study is also powered to demonstrate a difference in ADR.

Exploratory—and, importantly, separate—sample size calculations for MAP and ADR indicate that a larger sample would be required to detect a significant difference in ADR than in MAP; COLO‐DETECT has therefore been powered to detect a clinically meaningful and statistically significant difference in ADR, which exceeds that required to detect such a difference in MAP. This represents a difference of 7% in ADR (with a clinically meaningful difference deemed to be 10% for screening patients and 5% for symptomatic patients). Assuming a mixed sample of 40% screening (BCSP) patients and 60% symptomatic patients, with a baseline ADR of 27.6% across the sample (by aggregating BCSP and non‐BCSP data), a superiority design including 2032 participants will be required to provide 90% power for a two‐sided test for difference in proportions with an alpha value of 0.05. Allowing for 10% attrition due to incomplete colonoscopies, the target sample size will be 1828 participants having a complete colonoscopy. This sample size will more than enable detection of a pooled difference of 0.18 mean difference in MAP.

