### Data analysis

A full statistical analysis plan will be developed prior to analysis commencing. Statistical analysis will be performed by NWORTH CTU. The trial statistician and chief investigator will remain blinded throughout the trial and data analysis. The primary outcome, MAP in GGC versus SC, will be analysed using an ANOVA, using the randomization stratification variables as factors. The key secondary outcome, ADR, will be analysed using logistic regression, forcing trial arm into the model and including randomization stratification variables as factors. This approach will also be used to analyse the detection rate of SSPs, advanced adenomas and cancer, as well as caecal intubation rate, and effects on future colonoscopy workload. Subgroup analyses will be conducted on colonoscopist type (i.e., non‐BCSP accredited vs. BCSP accredited) and indication for colonoscopy (screening vs. symptomatic).

Whether group difference (GGC vs. SC) exists for the nature, morphology, and distribution of polyps found in the colorectum, will be analysed using a multinomial logistic regression; polyp size will be analysed using an ANOVA, as will whether group difference (GGC vs. SC) exists for withdrawal times (in procedures where no polyps were found), insertion time to the caecum (or limit of examination where the caecum is not reached), MPP and patient experience (measured using the Newcastle ENDOPREM™).

To identify changes in MAP and ADR over the time of the study (which might occur due to the trial progression effect [46]), detection rates for the first 20% of participants will be compared with those for the last 20% of participants for each colonoscopist, using repeated measures *t* tests and visual plots. Parallel data on reported detection rates amongst a selection of colonoscopists from the same units but not participating in the study will be compared with the measures obtained in the SC group.

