Additional strengths are the prospectively planned economic evaluation, to which the secondary objectives of measuring any differences in surveillance interval and the rates of AEs will make key contributions; and a process evaluation which will seek to understand issues relevant to the implementation of this technology across clinical practice, should it prove to be clinically effective.

Furthermore, COLO‐DETECT has included comprehensive patient and participant representative involvement, along with expert independent CTU statistician input into relevant aspects of study design and analysis (for which they will remain blinded), providing further methodological rigour. The unavoidable weakness of the study is an inability to achieve participant or colonoscopist blinding due to the nature of the intervention. However, this will affect all clinical studies of this type.

In conclusion, COLO‐DETECT will study the effectiveness of a novel technology in improving detection at colonoscopy along with cost effectiveness and process issues around uptake and utilization. The results will have a significant impact on future adoption of this novel technology.

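### The cancer detection rate counts lesions that an unblinded colonoscopist only suspects are cancer, with no confirmation required

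*Protocol article*

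**What the plan says.** Box 2, under Study objectives in the protocol article, lists the cancer detection rate among the other secondary objectives and says in brackets what it covers. There are two routes:

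- Route 1: "this includes polyps removed at colonoscopy and subsequently found to be cancerous".
- Route 2: "lesions felt to be cancerous at the time of colonoscopy".

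The Data analysis section carries the outcome into the logistic regression used for adenoma detection rate (ADR): "This approach will also be used to analyse the detection rate of SSPs, advanced adenomas and cancer". It adds no rule on confirmation.

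The Discussion concedes an "inability to achieve participant or colonoscopist blinding due to the nature of the intervention". The Data collection section puts histology of biopsies and of retrieved polyps on the case report form. Of the review at days 14 to 21, the Study process section says: "This may include accessing medical records (including endoscopy reports and histology".

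**The concern.** Route 1 depends on a later finding. Route 2 is complete when the procedure ends and rests on impression alone. A lesion that looks malignant and turns out to be benign therefore stays in the numerator. The person making that call knows which arm the participant is in, and the blinding of the trial statistician cannot correct a call made at the procedure.

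Cancers will be few compared with adenomas, so a handful of misclassified lesions can move the ratio visibly. A difference in cancer detection is also a result that readers would notice, even from a low-ranked outcome.

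**Working it through.** **1. The plan's own figure, and whether it is affected.** Inputs from Sample size: "with a baseline ADR of 27.6% across the sample"; "This represents a difference of 7% in ADR", so 27.6% against 34.6%; "90% power for a two‐sided test for difference in proportions with an alpha value of 0.05". With unpooled variance,

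n per arm = (1.960 + 1.2816)² × (0.276 × 0.724 + 0.346 × 0.654) / 0.07² = 10.507 × 0.4261 / 0.0049 = 913.7, rounded up to 914.

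That gives 1828 in total, and 1828 / 0.9 = 2031.1, or 2032 as an even number. Both stated figures reproduce. (Pooled variance gives 1834 and 2038.) No cancer rate enters the calculation, so the sample size does not depend on this definition.

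**2. The passages side by side.**

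| Place | What it settles |
|---|---|
| Box 2, route 1 | Counts after a later finding of cancer |
| Box 2, route 2 | Counts on impression at the procedure |
| Data collection | Histology of biopsies and retrieved polyps is recorded |
| Study process | The day 14 to 21 review may look at histology |
| Data analysis | Compares cancer detection by arm, with no confirmation rule |
| Discussion | The colonoscopist is not blinded |

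Histology is recorded, but no passage links it back to the route 2 count.

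**3. Illustration: equal false calls.** The article gives neither a cancer rate nor a false-call rate, so every rate from here on is assumed. Take true rates of 2% and 3%, a ratio of 3.0 / 2.0 = 1.50. Add false calls of 0.5% in each arm: 3.5 / 2.5 = 1.40. The ratio is pulled towards 1. With equal true rates the type I error stays at 5%.

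**4. Illustration: unequal false calls.** Take 914 per arm and the same true rate in both arms. With a and b the observed rates,

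chance of p < 0.05 = Φ(d/se − 1.96) + Φ(−d/se − 1.96), where d = b − a and se = √{[a(1 − a) + b(1 − b)] / 914}.

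Worked row: true rate 2%, false calls 0.5% (standard) and 1.0% (GI Genius). Then a = 0.025, b = 0.030, se = √(0.053475 / 914) = 0.00765 and d/se = 0.654, so the chance is 0.096 + 0.004 = 0.10.

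| True rate, both arms | 0.5% v 0.5% | 0.5% v 1.0% | 0.5% v 1.5% |
|---|---|---|---|
| 2% | 5% | 10% | 24% |
| 3% | 5% | 9% | 19% |
| 5% | 5% | 7% | 15% |

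**5. Set against sampling error.** With 1016 randomized per arm (2032 / 2) and an assumed 2% to 3%, there are about 20 to 30 cancers per arm. The approximate 95% interval around a true ratio of 1 is exp(±1.96 × √(2/20)) = 0.54 to 1.86 with 20 events, and exp(±1.96 × √(2/30)) = 0.60 to 1.66 with 30. Two to five false calls, all in one arm, would move the ratio by between 32/30 = 1.07 and 25/20 = 1.25, well inside those intervals.

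**The case against.** The strongest reply is that Box 2 is a list of objectives, and the bracket may only name the two ways a cancer comes to light: unexpected malignancy in a removed polyp, and an overt lesion seen at the procedure. Confirmation would then be left to the full protocol or analysis plan, and an article is not at fault for leaving out such detail. This reading is possible. But the text does state what counts, and it contrasts a later finding with an impression. If confirmation is intended, the wording still needs correcting.

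Parts of the objection stand in full, and they rule out stronger readings that a reader might infer:

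- *That the device inflates cancer calls in its own arm.* The introduction describes GI Genius as marking potential abnormalities, with the colonoscopist deciding what to do. Nothing says that the box signals malignancy, so neither the existence nor the direction of a difference in false calls is established.
- *That the impression route is superfluous because histology is already in hand.* Surgical resection specimens are not on the data collection list, active follow-up stops at days 14 to 21, and long-term record access depends on consent and, for some sources, on linkage that is not yet possible. A histology-only rule confined to that window could lose true cancers.
- *That the economic evaluation is compromised.* Lifetime modelling is to include effects on colorectal cancer, but the article does not say that it uses this count.

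**Conclusion.** The point holds as a fault in a stated definition. As written, an unconfirmed impression by an unblinded operator scores as a cancer in a between-arm comparison, and benign histology does not remove it.

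The consequence is limited. One other-secondary outcome is affected; mean adenomas per procedure (MAP), ADR and the sample size are not. Equal false calls dilute a true ratio. Bias between arms needs false calls that differ by arm, for which the article gives no figure. The 7% to 10% and 15% to 24% error rates above rest wholly on assumed rates, and the shifts are smaller than the sampling error of so sparse an outcome. The case for change is that the correction is cheap, not that a large bias has been shown.

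**What to change.** Define cancer detection as malignancy in a lesion found at the study colonoscopy, confirmed either on histology (polyp, biopsy or, where the records hold one, resection specimen) or by a documented cancer diagnosis in the medical records. Reclassify suspected lesions with benign final histology as non-cancer. Report colonoscopist-suspected lesions separately by arm, including those without tissue confirmation, and add a sensitivity analysis that counts the unconfirmed ones as cancers.

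The cost is one definition change. Most of the confirmation can come from histology already on the case report form or open to the day 14 to 21 review. A few suspected lesions will need a later records check, subject to participant consent, and some may stay unresolved; the separate report and the sensitivity analysis keep those visible.
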